## Abstract

**Background:**

Digital health programs, which encompass the subsectors of health information technology, mobile health, electronic health, telehealth, and telemedicine, have the potential to generate “big data.”

**Objective:**

Our aim is to evaluate two digital health programs in India—the maternal mobile messaging service (Kilkari) and the mobile training resource for frontline health workers (Mobile Academy). We illustrate possible applications of machine learning for public health practitioners that can be applied to generate evidence on program effectiveness and improve implementation. Kilkari is an outbound service that delivers weekly gestational age–appropriate audio messages about pregnancy, childbirth, and childcare directly to families on their mobile phones, starting from the second trimester of pregnancy until the child is one year old. Mobile Academy is an Interactive Voice Response audio training course for accredited social health activists (ASHAs) in India.

**Methods:**

Study participants include pregnant and postpartum women (Kilkari) as well as frontline health workers (Mobile Academy) across 13 states in India. Data elements are drawn from system-generated databases used in the routine implementation of programs to provide users with health information. We explain the structure and elements of the extracted data and the proposed process for their linkage. We then outline the various steps to be undertaken to evaluate and select final algorithms for identifying gaps in data quality, poor user performance, predictors for call receipt, user listening levels, and linkages between early listening and continued engagement.

**Results:**

The project has obtained the necessary approvals for the use of data in accordance with global standards for handling personal data. The results are expected to be published in August/September 2019.

**Conclusions:**

Rigorous evaluations of digital health programs are limited, and few have included applications of machine learning. By describing the steps to be undertaken in the application of machine learning approaches to the analysis of routine system-generated data, we aim to demystify the use of machine learning not only in evaluating digital health education programs but in improving their performance. Where articles on analysis offer an explanation of the final model selected, here we aim to emphasize the process, thereby illustrating to program implementors and evaluators with limited exposure to machine learning its relevance and potential use within the context of broader program implementation and evaluation.

**International Registered Report Identifier (IRRID):**

DERR1-10.2196/11456

## Introduction

Machine learning is an application of artificial intelligence that aims to allow computers to learn automatically from the analysis of large, highly granular datasets, with minimal human intervention [1]. In machine learning, models are created using existing data to make predictions about future events. Applications of machine learning in global public health are emerging, particularly in the context of digital health solutions, which have the potential to generate “big data.” Digital health encompasses the subsectors of health information technology, mobile health (mHealth), electronic health (eHealth), telehealth, and telemedicine.

Machine learning approaches in digital health have been mainly in the area of analyzing data generated by wearable sensors and accelerometers including efforts to predict and personalize monitoring systems for mobile patients [2], predict physical activity type and energy expenditure [3-5], and falls [6]. Beyond analyses of accelerometer data, studies have explored user engagement with different apps on mobile phones and tablets [7], and responses to patient feedback on health services [8]. Similar applications to social media data have sought to improve the detection of online illegal drug sales [9], depression [10,11], as well as explore vaccination sentiment trends and improve disease identification [12]. Analyses of geographic information system data have been used to map risk of exposure to disease [13]. Collectively these varied applications of machine learning have been classified by Mooney et al in three broad categories of (1) surveillance, including systems to monitor trends in disease incidence, health behaviors, and environmental conditions, (2) hypothesis-generating research, and (3) causal inference [1].

Evidence gathering on the effectiveness of digital health solutions is a growing field [14]. However, very few evaluations have sought to incorporate machine learning algorithms [8], and broader guidelines on the monitoring and evaluation of digital health solutions have stopped short of outlining options for predictive modeling [15]. Appropriate implementation of machine learning methodologies can facilitate dynamic, real-time interventions to improve data collection to assess program effectiveness and can also inform how data are used prospectively to improve program implementation.

In this paper, we outline methods proposed for the application of machine learning to the evaluation of two large-scale mHealth initiatives in India, which have scaled up to over 13 states in India since their initiation in 2012-2013. Kilkari is an outbound service that delivers weekly gestational age–appropriate audio messages about pregnancy, childbirth, and childcare directly to families on their mobile phones, starting from the second trimester of pregnancy until the child is one year old. Accredited social health activists (ASHA) mobilize women in the community to attend outreach and primary health center activities where auxiliary nurse midwives collect and register details of mothers and their pregnancies and, after delivery, children born in their catchment areas. Mobile Academy is an interactive voice response (IVR) audio training course for ASHAs in India. The training material delivered over the phone is designed to refresh their knowledge of life-saving preventative health behaviors and improve their interpersonal communications skills.

Through the use of these two digital health examples—the maternal mobile messaging service (Kilkari) and the mobile training resource for frontline health workers (Mobile Academy)—we illustrate possible applications of machine learning that can be applied to generate evidence on effectiveness, as well as to more broadly improve program implementation. We intend this paper to be an easy reference for public health practitioners considering the applicability of machine learning for digital health solutions, rather than a comprehensive review of the field of machine learning. In the course of the paper, we seek to provide an explanation in layman’s terms of the methods under consideration, for an audience unfamiliar with machine learning algorithms or advanced statistical methodologies. We also provide references throughout the text for further in-depth reading. Textbox 1 outlines the possible research questions that can be addressed by the study.

Study aims.Aim 1: Describe subscriber losses at different points during pregnancy and postpartum period from the programObjective 1a. Determine differences in subscribers who remain subscribed to Kilkari throughout the duration of service versus those lost at different points along the continuum of program databases.Objective 1b. Develop a classifier for identifying different categories of losses.Aim 2: Facilitate the program’s ability to identify and target ASHAs likely to perform poorly on digital health training programs and knowledge assessmentsObjective 2a. Determine predictors of training course completion (overall and time to completion) by ASHAs based on performance on early modules of the course and other characteristics including reported motivation, knowledge, individual characteristics, and mobile literacy.Objective 2b. Develop a classifier for the routine identification of ASHAs likely to perform poorly.Aim 3: Understand the factors underpinning successful receipt of calls (are calls received?)Objective 3a. Determine what proportion of calls successfully reach the end-user’s device for Kilkari.Objective 3b. Identify the proportion of content specific to infant feeding and family planning received by end-users for Kilkari.Aim 4. Determine how users are listening to messagesObjective 4a. Determine predictors for exposure to Kilkari content based on user characteristics.Objective 4b. Measure exposure to Kilkari content based on technological and behavioral (end-user engagement) performance.Objective 4c. Develop a classifier for measuring listening levels.Aim 5: Understand optimal message delivery options for maximal impactObjective 5a. Determine message delivery options with the most success in engaging client and assess patterns of listening.Objective 5b. Determine the effect of early listening patterns (time of day of listening, duration and frequency of listening, content listening patterns) on postpartum engagement and overall exposure.

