### Data Processing

For the Kilkari program, the pregnant women or postpartum women’s data are captured in the RCH and MCTS systems, or in state-based systems that then pass data to RCH or MCTS, and from there to the MOTECH system. Before the data are accepted by MOTECH, the system automatically runs validations to check that the mobile numbers are in the correct format, locations match location masters in the MOTECH database, and last menstrual period and date of birth are within the Kilkari timeframe. The MOTECH system uses the last menstrual period or the delivery date to determine the schedule of messages to be delivered. The MOTECH engine provides the list of phone numbers (clients) to be called each day to the IVR system, which then calls the numbers and plays the appropriate pre-recorded message, which is stored in the IVR system’s content management system. If the call is not answered, then the IVR system attempts to call again at least 3 times every day for 4 days until the call is answered.

For the Mobile Academy program, details on ASHAs including their names, phone numbers, geographic location, and age are contained in either the RCH or MCT databases, or in state-based databases integrated with MCTS and used to register them to Mobile Academy. The MOTECH engine captures these data on ASHAs from the RCH or MCTS databases and following registration to Mobile Academy, ASHAs are eligible to call in to the IVR system using the same phone number provided in the RCH database. The IVR system validates the phone number against the MOTECH system and then retrieves the “bookmark” information that details the status of the ASHA and her progress on the list of content expected to be covered. Based on this information, the appropriate content is delivered to the ASHA via the IVR system and the updated data return to the MOTECH database.

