## Discussion

### Principal Considerations

This paper presents the testing of a range of machine learning approaches to be incorporated as part of the evaluation of two large digital health programs in India—Mobile Academy and Kilkari. By utilizing machine learning approaches, we aim to improve the use of data for generating evidence on program reach and exposure as well as factors underpinning uptake for both programs. We will start by measuring dropped cases and missing data along the continuum of the databases. As part of this analysis, we aim to understand differentials in the characteristics of individuals lost along the continuum of databases and in turn, missed by the Mobile Academy or Kilkari programs. We then consider the technological performance as captured by four stakeholders: (1) government data systems (MCTS, RCH, webservices), (2) program’s call delivery and receipt systems, (3) mobile network operator (network coverage and quality), and (4) user device characteristics (switched on, within range of network). Finally, we explore user engagement with the program (behavioral performance) including patterns in the data that could predict key program performance metrics, including training completion for Mobile Academy and user coverage and exposure for Kilkari.

Analyses to measure dropped cases and missing data along the continuum of the databases, starting with the MCTS and RCH databases, are anticipated to generate insights into user relay of information to the Government of India including the provision of phone numbers by health workers and women. At present, there are no reliable estimates of the proportion of pregnant women with accurate mobile numbers, last menstrual periods, or dates of birth (for themselves or child) covered by the databases. More broadly, these analyses will help improve understanding of the quality of the RCH and MCTS data and underlying sampling frames used for Mobile Academy, Kilkari, and a range of other programs, including the characteristics of individuals included compared to those excluded. The predictors identified will help identify groups of women who are more likely to be missed by the program and ASHAs less likely to complete their course. These findings will also be used to inform the sampling of respondents for qualitative research to explore issues in depth and possibly identify opportunities for improving program targeting like registration of users.

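### Objective 1a compares losses at every database stage with women who stayed subscribed to the end, so predictors of later drop-out can appear as, or hide, predictors of early loss

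*Protocol article*

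**What the plan says.** The study aims textbox in the Introduction of the Protocol article defines Objective 1a as determining differences in "subscribers who remain subscribed to Kilkari throughout the duration of service versus those lost at different points along the continuum of program databases". Objective 1b follows: "Develop a classifier for identifying different categories of losses". It names no reference group and no set of records at risk.

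The losses occur in sequence. The Data Processing section has records pass from RCH or MCTS (some by way of state systems) to MOTECH, and adds: "Before the data are accepted by MOTECH, the system automatically runs validations". The checks cover number format, location and dates. Table 1 then lists activation and deactivation dates as MOTECH elements. A record can therefore be lost before any subscription exists, or after activation.

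Under Principal Considerations, the Discussion restates the analysis: "we aim to understand differentials in the characteristics of individuals lost along the continuum of databases". For the RCH and MCTS data and the sampling frames drawn from them, it also plans a description "including the characteristics of individuals included compared to those excluded". On use, it says: "The predictors identified will help identify groups of women who are more likely to be missed by the program".

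**The concern.** Women who stay for the full service have passed validation, been activated, and then stayed subscribed through pregnancy, the postpartum period or both. As the reference for loss at an early stage, they are selected on everything that happens afterwards. The women who passed the early stage but dropped out later are missing from the comparison, although they are evidence of who gets through that stage.

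The contrast therefore mixes two questions: who is lost at this stage, and who among those passing it stays to the end. If a characteristic is related to the second, the answer to the first shifts.

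This matters because the Discussion uses the predictors to find groups likely to be missed, to choose respondents for qualitative work and possibly to improve registration. A group whose real difficulty is later drop-out could be taken to have a registration or data-quality problem, or a real gap at validation could go unseen. A larger dataset does not help; it only estimates the mixed contrast more precisely.

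**Working it through.** **Inputs.** The plan states no loss rates for Aim 1, so there is no figure to reproduce. The Discussion itself notes: "At present, there are no reliable estimates of the proportion of pregnant women with accurate mobile numbers". All rates below are assumptions.

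**Set-up.** Take a binary characteristic X and two sequential stages. Let e1 and e0 be the loss at the early stage for X = 1 and X = 0. Let l1 and l0 be the later loss among those who passed the early stage.

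- Early loss vs all who passed the stage: OR_pass = [e1/(1 − e1)] / [e0/(1 − e0)].
- Early loss vs full-duration subscribers: OR_full = {e1/[(1 − e1)(1 − l1)]} / {e0/[(1 − e0)(1 − l0)]}.
- Hence OR_full = OR_pass × (1 − l0)/(1 − l1).

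The multiplier depends only on later retention. It equals 1 when l1 = l0, whatever the early loss rate.

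**No true early association (e1 = e0, OR_pass = 1.00).** The results are the same at early loss of 10%, 30% and 50%.

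| Later loss, X = 0 | Later loss, X = 1 | Multiplier | OR_full |
|---|---|---|---|
| 20% | 20% | 0.80/0.80 | 1.00 |
| 20% | 30% | 0.80/0.70 | 1.14 |
| 40% | 60% | 0.60/0.40 | 1.50 |
| 20% | 50% | 0.80/0.50 | 1.60 |
| 50% | 80% | 0.50/0.20 | 2.50 |

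**Masking.** Take early loss of 30% for X = 1 and 40% for X = 0, with later loss of 50% and 20%. OR_pass = (0.30/0.70)/(0.40/0.60) = 0.64. OR_full = 0.64 × 0.80/0.50 = 1.03. The real difference disappears.

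**The same in shares of records.** Suppose 40% of records are rural and validation rejects 20% of both groups.

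- Rejected: rural 0.4 × 0.2 = 0.08; urban 0.6 × 0.2 = 0.12.
- Later retention of 30% rural and 50% urban leaves full-duration shares of 0.4 × 0.8 × 0.3 = 0.096 and 0.6 × 0.8 × 0.5 = 0.24.
- OR_full = (0.08/0.12)/(0.096/0.24) = 1.67, when the truth is 1.00.

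**Objective 1b on the same shares.** A single multi-class model trained on all records estimates the probability of each category given the characteristic. For validation loss that is 0.08/0.4 = 20% rural and 0.12/0.6 = 20% urban, so these predicted probabilities carry no distortion. It returns only if each loss group is modelled against full-duration subscribers alone.

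**The case against.** Several points against the concern stand, at least in part.

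- **Causation.** A reader might infer that later drop-out will be taken as a cause of early loss. The documents do not support that. Aim 1 is to describe losses, Objective 1a to determine differences, and the Discussion speaks of differentials and predictors.
- **The entry stage.** The comparison of included with excluded individuals in the Discussion is close to a lost-versus-passed contrast for RCH and MCTS. It partly covers entry, but it neither amends Objective 1a nor extends to later stages.
- **The classifier.** A reader might infer that Objective 1b inherits the defect. It names no comparator, and a multi-class model on all records would not.
- **The use.** A reader might take the results to show which database loses which group. The Discussion claims less: groups missed by the program overall, with improvements to targeting only a possibility.
- **Population.** Objective 1a speaks of subscribers, and a record rejected at validation never was one. The reference to the continuum of databases allows the wider reading; the text leaves this open.
- **Level of detail.** The Introduction calls the textbox a list of possible research questions, and the article condenses a fuller plan. Nothing excludes a stage-by-stage analysis, and the contrast with full-duration subscribers is legitimate as description. Yet the comparator is stated, not left open, and it is not the one that shows who is lost at a given stage.
- **Size.** The distortion depends on later loss varying with the characteristic, and no rates are given. But Objective 1a itself looks for such differences at later points, so the plan cannot assume there are none.

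**Conclusion.** The point holds as a matter of comparator choice. Objective 1a fixes one reference group for losses at sequential stages, and that group is selected on surviving all of them. The early-stage odds ratio is multiplied by the ratio of later retention. Under the assumed rates a true 1.00 becomes 1.14 to 2.50, and a true 0.64 can become 1.03. These are illustrations, not estimates for Kilkari, and the distortion is nil where later loss does not vary with the characteristic.

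The consequence is confined to which characteristics are reported as predictors of loss at a stage. It does not amount to a causal misreading, and it does not by itself invalidate the classifier. It is worth correcting because the Discussion puts the predictors to practical use and the correction is cheap.

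**What to change.** Add to Objective 1a that, at each stage, records lost at that stage are compared with all records that reached and passed it, whatever happened to them later. Keep the contrast with full-duration subscribers as an overall description.

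Two clarifications belong with it:

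- Report records rejected before MOTECH acceptance separately from losses of activated subscribers.
- Define the stages separately for records that enter in pregnancy and those that enter after childbirth. The Data Sources and Flow section describes capture at both times, and the Data Processing section schedules messages from either the last menstrual period or the delivery date. One chain from activation to birth would not fit every record.

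For Objective 1b, state that the classifier is trained either per stage on the records at risk there, or as one multi-class model on all records and read through its predicted probabilities. It should not be built as each loss group against full-duration subscribers alone.

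The cost is wording and some further comparisons on data the plan already intends to extract. The downside is several stage-specific results to report in addition to one contrast.

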### Additional Data From Baseline Surveys of Evaluation of Kilkari and Mobile Academy

Analyses described in this section are being carried out as part of a larger external evaluation of Kilkari. We describe concurrent efforts to undertake a randomized controlled trial (RCT) in the state of Madhya Pradesh (MP) for Kilkari, inclusive of baseline surveys with pregnant and postpartum women, and ASHA workers. Once identified as part of baseline survey activities and randomized to receive Kilkari content (or no content at all), phone numbers will be fed directly into the MOTECH database for provision of program services. For pregnant women, additional data collected as part of baseline household surveys include demographic factors (age, education, parity, literacy), socioeconomic characteristics (household assets, conditions), health care seeking and practices, as well as data on digital literacy and phone access. These data can be linked to MOTECH, IVR, and call center records to provide additional data elements. Overall, these data as well as data on technology performance (receipt of messages) and user engagement (behavioral performance) with content will help estimate exposure to Kilkari used in the assessment of causality as part of the RCT. For ASHAs, baseline survey data will include similar data elements on demographic, socioeconomic, and mobile literacy and phone access as well as knowledge and work-related variables linked to reported motivation and satisfaction. Overall, these added data elements can be linked to IVR and call record data for this subpopulation of Mobile Academy and Kilkari users in four districts of MP where the RCT is underway.

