#### Splitting Into Training and Testing

To avoid overfitting models that work well for the data in hand but fail to predict well with other datasets, the data will be split into three components. This is possible due to the large size of the dataset. The training set will comprise 60%, the test dataset 20%, and the validation dataset 20% of the data. The test set will be used to test and fine-tune the accuracy of predictive models, and the final selected model will be applied to the validation dataset. We anticipate having data from 2017, 2018, and 2019 and will ensure equal representation by random sampling. To ensure that the data are controlled for time as a confounder, subsets will be equally represented across different time periods.

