Analyses to understand the technological performance of the program will build off of those conducted on the MOTECH platform in Ghana [19] and of MomConnect in South Africa [8]. In the former, IVR message delivery trends suggested that 25% or less of expected mobile health information messages were received by pregnant women [19]. While 20% delivery rates of successful outbound dialing calls are standard in the mobile industry, limitations in the timeliness of problem identification represent a missed opportunity for improving program exposure using, for example, call retry logics and systems. In South Africa, over 80% of short messaging service (SMS) messages were successfully delivered as part of MomConnect. SMS as a delivery channel has a much higher success rate than outbound dialing calls but suffers from other weaknesses in countries where illiteracy rates are high and local language fonts are not widely available on devices. In the case of MomConnect, however, challenges in the use of unstructured supplementary service data meant that 26% of initiated registrations did not convert into successful registrants [8]. These two examples reinforce the need to understand the user journey and follow the flow of data to understand whether the technology performs as intended.

Beyond understanding the technological performance of the program, and the wider telecommunications network and device landscape that it operates within, analyses will aim to measure user engagement, including predictors for exposure to content based on user characteristics. In the context of Kilkari, we will additionally plan to explore the effect of early listening patterns (eg, time of day of listening, duration and frequency of listening, content listening patterns) as a predictor for postpartum engagement and overall exposure. For Mobile Academy, we will use a mixture of unsupervised and supervised machine learning techniques to generate predictors of training course completion by ASHAs based on performance on early modules of the course. These will be externally validated using a range of data elements on other ASHA characteristics obtained from the broader evaluation, including reported motivation, knowledge, individual characteristics, and mobile literacy.

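### Objective 2a: ASHA knowledge and motivation come from a survey that need not precede the Mobile Academy course, so in the survey-augmented Madhya Pradesh model these predictors may follow the outcome

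*Protocol article*

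**What the plan says.** In the Study aims textbox of the Introduction, Objective 2a is to find what predicts whether and how fast ASHAs finish the course, starting from how they do in its first modules. To these it adds "other characteristics including reported motivation, knowledge, individual characteristics, and mobile literacy". Objective 2b then asks for a classifier that routinely picks out ASHAs likely to do badly.

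The section on additional data from the baseline surveys gives the source of the non-system variables. For ASHAs the survey collects demographic, socioeconomic and phone-access items, "as well as knowledge and work-related variables linked to reported motivation and satisfaction". The same section describes the randomised trial as one of Kilkari in MP, and says that the survey items "can be linked to IVR and call record data for this subpopulation of Mobile Academy and Kilkari users in four districts of MP".

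The Introduction describes the course material as "designed to refresh their knowledge of life-saving preventative health behaviors". On dates, the section on splitting the data says "We anticipate having data from 2017, 2018, and 2019", the Analysis section says the horizon may be 2017-2018, and the Introduction places the start of the two programmes in 2012-2013. Table 1 lists course start and completion dates among the MOTECH fields.

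The Discussion (Principal Considerations) gives the survey variables another role. There, predictors of completion are derived from early-module performance, and "These will be externally validated using a range of data elements on other ASHA characteristics obtained from the broader evaluation".

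**The concern.** A predictor is useful for Aim 2 only if it is known before the outcome. The survey is called a baseline, but it is the baseline of the Kilkari evaluation. ASHAs enter Mobile Academy by registration through the government databases and then call in when they choose (Data Processing section), so nothing ties course start to the interview. The people to be linked are already described as Mobile Academy users, and the programmes predate the data window. It is therefore plausible that some had started or finished the course before they were interviewed.

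The course is meant to act on knowledge. For an ASHA interviewed after completing it, a higher score partly reflects completion. Knowledge could then appear to predict completion with no predictive value at enrolment, and the survey-augmented MP model would look better than it could perform prospectively. The 60/20/20 random split would not reveal this, because the training, test and validation sets would all contain the same mixture of interviews before and after the course.

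**Working it through.** The article gives no figure on this point, so there is nothing to reproduce. The check has two parts.

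**Time order, from the text**

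| Element | Where it is fixed | What follows |
|---|---|---|
| Outcome: completion, time to completion | Objective 2a | Dated in MOTECH |
| Predictors: knowledge, motivation | Objective 2a | Dated by the survey interview |
| Survey | Additional data section | Baseline of the Kilkari trial; no date given |
| Course acts on knowledge | Introduction | Reverse path for knowledge; nothing similar is said of motivation or satisfaction |
| Rule that the survey precedes the course | Not in the article | Order left open |

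**Possible size, under assumptions**

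Neither quantity below is in the article:

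- *d*: the knowledge gain from completing the course, in SD units, taken as 0.2, 0.5 and 0.8.
- *f*: the share of completers who finished before their interview, taken from 0 to 1.

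Suppose that knowledge before the course is N(0,1) in completers and non-completers alike (no true predictive value), and that non-completers gain nothing. A completer interviewed after the course then has knowledge N(*d*,1). The difference from a non-completer is N(*d*,2), so the probability that the completer scores higher is Φ(*d*/√2):

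- *d* = 0.2: Φ(0.141) = 0.556
- *d* = 0.5: Φ(0.354) = 0.638
- *d* = 0.8: Φ(0.566) = 0.714

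Completers interviewed before the course contribute 0.5. Hence

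AUROC = (1 − *f*) × 0.5 + *f* × Φ(*d*/√2).

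| *f* | *d* = 0.2 | *d* = 0.5 | *d* = 0.8 |
|---|---|---|---|
| 0 | 0.500 | 0.500 | 0.500 |
| 0.25 | 0.514 | 0.535 | 0.554 |
| 0.5 | 0.528 | 0.569 | 0.607 |
| 0.75 | 0.542 | 0.604 | 0.661 |
| 1 | 0.556 | 0.638 | 0.714 |

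A simulation with 200,000 ASHAs, half of them completers, agreed to within 0.002 at *f* = 0, 0.5 and 1.

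These are values for knowledge alone. If non-completers gain *g* from the modules they did take, the contrast falls. With everyone interviewed after their course activity, *d* − *g* replaces *d*, so *d* = 0.8 and *g* = 0.4 give Φ(0.4/√2) = Φ(0.283) = 0.61 instead of 0.71. Restricting the predictor to ASHAs interviewed first sets *f* = 0 and returns 0.50 for every *d*.

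**The case against.** The strongest reply is that the harmful order is not shown to occur. The article does not date the ASHA survey, does not say when Mobile Academy began in these four districts, and does not say how many surveyed ASHAs had already taken the course. This stands. A reader might infer from the 2012-2013 start and the 2017 data window that most were trained first, and so that Objective 2a will report a reverse-caused association. The documents make earlier training plausible but do not establish it.

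A second reply is that a date-ordering rule belongs in an analysis plan, and that the textbox lists questions the study could address. This stands only in part. The article itself fixes the predictors, their source and the linked population, and that combination admits predictors measured after the outcome. The Limitations section covers selection, confounding, listener identity and incomplete predictors, but not this.

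Third, the Discussion uses the survey variables for external validation and not as model inputs. That does not agree with Objective 2a. Validation against knowledge measured after the course would also have the same ordering problem.

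Two further stronger readings are tempting. One is that the routine classifier of Objective 2b would be inflated. The survey variables exist only for a subgroup in four MP districts, while the programmes run across 13 states, so they cannot be routine inputs. The other is that motivation and satisfaction are also changed by the course. The article says the course addresses knowledge and communication skills; it claims no effect on motivation or satisfaction.

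**Conclusion.** The point holds for the survey-augmented MP model only. As written, the plan allows knowledge measured after the course to count as a predictor of completing it, and for those ASHAs the association would be partly reverse-caused. For motivation and satisfaction, the defect is that they may be measured after the outcome.

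The size cannot be determined from the article. On the assumptions above, the spurious AUROC of knowledge alone runs from 0.50 (no completers trained earlier) through 0.53 to 0.61 (half) to 0.56 to 0.71 (all), and is smaller if non-completers also gain. Models built on system-generated data are untouched. The ordering should be settled before the survey variables are used, but it does not threaten the wider analysis.

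**What to change.** State the ASHA survey dates, and compare each interview date with the MOTECH course dates. Use survey knowledge, motivation and satisfaction as predictors only for ASHAs interviewed before course start. If prediction is to be made after the early modules, as Objective 2a suggests, the interview may instead be required to precede that landmark and completion. This keeps some ASHAs interviewed mid-course.

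For the remaining ASHAs, keep only fixed characteristics such as age and education, and report them separately. State whether the survey variables are predictors (Objective 2a) or external validation data (Discussion), and apply the same ordering in either role.

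The cost is a date comparison, using course dates already listed in Table 1 and the survey's interview dates, and a smaller MP subsample. How much smaller cannot be said until the survey dates are known.
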